### Outcomes assessment

2.2

All the outcomes will be assessed across three separate sessions, with a minimal interval of 48 h between each. On the first day, anthropometric measures and muscle size will be evaluated. The second day will focus on questionnaires and battery tests assessing disability, physical performance, frailty and muscle function. Finally, on the last day, questionnaires on cognitive function and the individual force-velocity (F-V) relationship on the leg press will be assessed. An overview of the outcomes that will be evaluated during this study is presented in Table 1.

**TABLE 1 T1:** Overview of the outcomes.

Outcome	Device/Procedure
Anthropometry and body composition	
Body mass, *kg*	Scale
Height, *m*	Stadiometer
Body mass index, *kg·m* ^ *−2* ^	​
Muscle size	Ultrasound
Anatomical cross-sectional area of the rectus femoris, *cm* ^ *2* ^	​
Anatomical cross-sectional area of the vastus lateralis, *cm* ^ *2* ^ Muscle volume of the vastus lateralis, *cm* ^ *3* ^	​
Sit-to-stand (STS) muscle power	Power frail app
Absolute muscle power, *W*	​
Relative muscle power, *W·kg* ^ *−1* ^	​
Allometric muscle power, *W·m* ^ *−2* ^	​
Force-velocity parameters	Leg press and linear position transducer
Theoretical maximal isometric force, *N*	​
Theoretical maximal unloaded velocity, *m·s* ^ *-1* ^	​
Maximal muscle power, *W*	​
Slope of the F-V relationship, *N·(m·s* ^ *−1* ^ *)* ^ *−1* ^	​
Physical performance	​
Short physical performance battery, *score*	Stopwatch
10-M walking, *m·s* ^ *-1* ^	Stopwatch
Timed up and go, *s*	Stopwatch
30-s STS, *rep*	Power frail app
10-s STS, *rep*	Power frail app
Disability in basic and instrumental activities of daily living	
Barthel index	Questionnaire
Lawton index	Questionnaire
Cognitive function	​
Mini-mental state examination, *score*	Questionnaire
Frailty	See text for details
Fried frailty phenotype, *criteria*	​
Frailty trait scale short form, *score*	​

Abbreviation: F-V, force-velocity, STS, sit-to-stand.

#### Anthropometric measures and muscle size

2.2.1

Anthropometric measures will include body mass, height, and body mass index (BMI) using a portable scale (Rowenta BS1500, Erbach, Germany) and stadiometer (Seca 213, Hamburg, Germany).

The anatomical cross sectional area (ACSA) of the vastus lateralis (VLa) and rectus femoris (RF) muscles will be assessed using a B-mode ultrasonography (GE Healthcare, LOGIQ F6, Chicago, Illinois) with a linear-array probe (50-mm field of view, 12 MHz). Resting ultrasound images will be collected with the participants in the supine position with their knees over a foam roller resting slightly flexed at 150° (180° = full knee extension) (Pareja-Blanco et al., 2020). After 15 min in the described position, VLa and RF ACSA will be measured at 35%, 50%, and 65% of the femur distance between the superior border of the greater trochanter (0% of the distance) and the inferior border of the lateral condyle (100% of the distance) of the right leg (Pareja-Blanco et al., 2020). These thigh lengths were found to be valid and highly repeatable to measure quadriceps femoris ACSA (Hernández-Belmonte et al., 2022b). Adhesive gaskets will be fixed to the skin at the predetermined site along the transverse measurement path to facilitate gel application and ensure a rectilinear trajectory. A panoramic image will be acquired by an experienced researcher (>200 h of ultrasonography practice), keeping the probe perpendicular to the surface of the skin and applying a minimum pressure not to compress the tissues (Hernández-Belmonte et al., 2022a). The location of the measurement points will be confirmed by documenting the probe positions on transparent sheets (Alegre et al., 2015).

The muscle ACSA will be measured by manually tracing the aponeurosis of the RF and VLa muscles (ImageJ v1.53a; National Institutes of Health, Bethesda, MD). The average ACSA value (in cm^2^) obtained from two images will be considered for further analysis (note: a third image will be analyzed when the coefficient of variation is higher than 5% (Pareja-Blanco et al., 2020; Hernández-Belmonte et al., 2023b). Additionally, muscle volume of the VLa muscle will be estimated from the VLa ACSA obtained at 35%, 50% and 65% of the femur length and insertion points of the VLa muscle in the femur (5% and 80% of the femur length) (Hogrel et al., 2015). This approach has been previously validated by Cornejo-Daza et al. (2024).

#### Sit-to-stand muscle power

2.2.2

Muscle function will be assessed by the STS muscle power test (Alcazar et al., 2018). Mean power produced by the participants during the 5-repetition, 10-s and 30-s STS tests will be calculated using a validated equation incorporated into the “Power Frail” smartphone app (Alcazar et al., 2018):
$$Absolute\;muscle\;power\;\left(W\right)=\left(Body\;mass\cdot 0.9\cdot g\right)\cdot \frac{\left(\left[Body\;height\cdot 0.5\right]-Chair\;height\right)}{\left(\frac{\;STS\;time}{number\;STS\;reps}\right)\cdot 0.5}$$

Relative muscle power (i.e., normalized to body mass) and allometric muscle power (i.e., normalized to body size) will be calculated as follows:
Relative muscle power (W·kg)−1=Absolute muscle powerBody mass

Allometric muscle power (W·m)−2=Absolute muscle powerBody height squared

#### Force-velocity relationship in the bilateral leg press exercise

2.2.3

The individual F-V relationship will be evaluated on a horizontal leg press (Selection MD, Technogym, Italy) using a linear position transducer (Chronojump, BoscoSystem, Barcelona, Spain) coupled to the machine (Sousa et al., 2024). The standardized procedure to assess the F-V relationship in older adults has been published elsewhere (Alcazar et al., 2017).

First, two familiarization sessions will be carried out to ensure the participants are able to perform the correct exercise technique. Additionally, the starting position on the leg press machine will be individually identified to reproduce the same range of movement in all assessments and exercise sessions. All participants will be with their feet placed on the leg press feet platform, back in contact with the seat, knee and hip joints with a comfortable angle of 90°–110° (180° = full extension), and both hands gripping the side handles.

Before testing, the participants will perform a standardized warm-up including 5-min of walking at comfortable speed and 1 set of 8 repetitions on the leg press with a load equivalent to 40% of their body mass. The intended velocity will be progressively increased until conducting the last 3 reps at maximal intentional velocity. The F-V relationship will be assessed through a progressive test with at least three incremental loads until reaching 75–85%F0. The loads that did not comply with physiological principles will be discarded (Alcazar et al., 2023). The recovery time between sets will be imposed according to the mean velocity exerted by the subjects in the preceding repetition (>0.30 m·s^− 1^: 60 s; 0.30–0.20 m·s−^1:^ 90 s; <0.20 m·s^− 1^: 120 s). The subjects will be continually encouraged to perform each repetition as fast and strongly as possible. The highest mean velocity attained with each load will be considered for the analysis. A linear F-V equation will be fitted over F-V data comprised between 45% and 100% of F_0_ (Alcazar et al., 2021b). Several outcomes will be extracted from the F-V relationship (Alcazar et al., 2017): F_0_, maximal unloaded velocity (V_0_), slope of the F-V relationship, and maximal muscle power (Pmax). The F-V relationship analysis and the resulting variables are illustrated in Figure 2.

**FIGURE 2 F2:**
[figure not shown]
Excel-template to create the individual force–velocity (F–V) relationship in the bilateral leg press from linear position transducer data. The Excel files and instructions are publicly available at: https://github.com/[name]/F-V-profiling.

#### Physical performance

2.2.4

The Short Physical Performance Battery (SPPB) (Guralnik et al., 1994) will be used to evaluate lower-limb physical function using three components: static balance, 4-m habitual gait speed, and 5 repetitions STS performance. For static balance, participants are instructed to stand in three different positions (feet together, semi-tandem, and full tandem) for a maximum of 10 s each. To assess gait speed, participants begin from a static position behind a line marked on the floor and walk at their usual pace toward a target located 4 m away; the test ends when they cross the target line. The time taken to complete the distance is recorded, and gait speed is calculated accordingly (m·s^-1^). For the STS test, participants start seated on a chair and perform 5 STS repetitions as quickly as possible without arms assistance. Each repetition requires contact with the seat prior to standing up again. Based on the results in each component, this battery is scored from 0 (worst) to 12 (best) with a maximum of 4 points assigned to each domain: balance, gait speed, and STS performance (Guralnik et al., 1994).

The 10-m walking test (Rossier and Wade, 2001) will be used to assess the time required to walk 10 m at maximum speed. The subjects start from a static position and walk in a straight line to complete the established distance in the shortest time possible. Maximal gait speed is calculated by dividing the distance by the time (m·s^-1^).

The Timed Up and Go test (Herman et al., 2011) will measure the time it takes the participants to (i) stand up without using their arms, (ii) walk 3 m, and (iii) turn around and sit down again. This test has been proposed for measuring agility (i.e., dynamic balance) in institutionalized older adults (Buendia-Romero et al., 2023) and as a strong predictor of fall risk among older adults (Lusardi et al., 2017).

In addition, the participants will complete the 10-s and 30- STS tests. Participants will start seated on a chair and will perform as many full STS repetitions as possible within the allotted time without arms assistance (Alcazar et al., 2020).

All tests will begin with the standardized cue “3, 2, 1, go”. Two attempts, with a rest of 1–3 min, will be allowed for each test, and the best performance will be considered for analysis. A stopwatch will be used to record the time required for timed tests and to control the duration of time-limited protocols.

#### Disability in basic and instrumental activities of daily living

2.2.5

Disability in basic and instrumental ADL will be assessed using the Barthel index (Mahoney and Barthel, 1965) and Lawton index (Lawton and Brody, 1969). The Lawton questionnaire assesses the ability to use the telephone, shopping, cooking, household duties, laundry, use of transportation, responsibility for their medication, and handling of economic matters. Each item is assigned a numerical value (1 = independent, 0 = dependent), therefore, the maximum dependence would be marked by obtaining 0 points and total independence by obtaining 8 points. The Barthel index is a 10-item questionnaire that provides information about the autonomy to cook food, wash, dress, groom, perform bowel movements and urination, go to the toilet, move from the bed to the chair, walk and climb stairs. The total score ranges from 0 to 100, with higher scores indicating greater independence and lower scores indicating higher levels of dependence in basic daily activities.

#### Cognitive function

2.2.6

Cognitive function will be assessed using the Mini-Mental State Examination (MMSE) questionnaire (Folstein et al., 1975). The MMSE comprises 11 items that measure attention and orientation, memory, registration, recall, calculation, language, and the ability to draw a complex polygon. The total score ranging from 1 (lowest cognitive function) to 30 (highest cognitive function) points.

#### Frailty

2.2.7

The Frailty Trait Scale short form (FTS-5) (García-García et al., 2020) and Fried’s Frailty Phenotype (FP) (Fried et al., 2001) will be used to assess frailty syndrome. FTS-5 evaluates five domains: BMI, Physical Activity Scale for the Elderly (PASE) questionnaire, handgrip strength, Romberg static balance test and gait speed in the 3m walking test. Each FTS-5 component is scored from 0 to 10, yielding a total score ranging from 0 to 50. Participants scoring ≤25 points will be classified as robust, whereas those scoring >25 points will be classified as frail (García-García et al., 2020). FP includes 5 criteria: involuntary loss of ≥4.5 kg in the prior year, self-reported exhaustion, weakness (i.e., low handgrip strength), low habitual gait speed in the 4.5-m walking test and low physical activity measured through the PASE questionnaire. Participants will be classified as robust (0 criteria), pre-frail (1 – 2 criteria) or frail (3–5 criteria) (Fried et al., 2001).

### Velocity-based resistance training program

2.3

The intervention will consist of a VBRT program performed in the bilateral leg press exercise (Selection MD, Technogym, Italy). The exercise sessions will be conducted twice a week (interspersed by at least 48 h) during a total of 9 months (note: 29 active weeks after excluding assessment weeks and vacation breaks). The leg press exercise has been previously demonstrated to be an effective and safe strategy for improving muscle function in frail, institutionalized and hospitalized older adults (Cadore et al., 2014a; Losa-Reyna et al., 2019; Ferrara et al., 2025). Each session will begin with a ∼10-min warm-up consisting of a 4-min walk at usual gait speed and dynamic balance exercises (zig-zag walking, stepping over obstacles, lateral displacements, and changes of direction). For the main part of the exercise session, the participants will perform either 4 sets (for those allocated in to the 10% VL group) or 3 sets (for those allocated into the 20% VL group) at 60% of F_0_ in the leg press exercise (except for the first week, for which the intensity will be set at 50% of F_0_). The number of sets for each VL group was selected after pilot testing so both groups will perform a similar total number of repetitions in each exercise session. The load corresponding to 60% of F_0_ will be adjusted individually for each exercise session by the monitoring of repetition velocity (Chronojump, Bosco System, Spain) (González-Badillo et al., 2022). Therefore, the absolute load will be decreased when the participants exhibit a mean velocity in the fastest repetition below the target velocity for 60% of F_0_, and the load will be increased when mean velocity in the fastest repetition is higher than the target velocity for 60% of F_0_. The fastest repetition in each set will be used as the reference velocity for controlling intensity and VL, according to previous studies using VBRT (García-Ramos et al., 2021; Sousa et al., 2025). A threshold based on the standard error of measurement (SEM) of mean velocity at 60%F_0_ obtained from our sample in a pilot reliability study (SEM = 0.023 ± 0.004 m·s^-1^) will be considered for increasing or decreasing the load until reaching the target velocity. Similarly, movement velocity will be monitored during the set, and the participants will complete consecutive repetitions until reaching the target intra-set fatigue (i.e., VL threshold) (Sánchez-Medina and González-Badillo, 2011). The participants will be encouraged to perform the concentric phase of each repetition as fast as possible. The eccentric phase will be completed at a 2–3-s pace in order to ensure the reliability of the concentric velocity measurements and to control the physiological adaptations associated with different eccentric durations (Handford et al., 2022). A brief pause (∼1 s) will be imposed between the eccentric and concentric phases. A 3-min rest will be allowed between sets. All sessions will be performed at the same time of the day for each subject (±2 h) and under similar environmental conditions, and will be supervised by qualified strength and conditioning coaches (MSc in Sport Sciences). Attendance will be recorded throughout the intervention.

### Follow-up

2.4

After the 9-month intervention period, participants only will receive their usual care for a 6-month follow-up period. Usual care will include nursing care, physiotherapist assistance, medical attention, and participation in recreational activities with no structured physical exercise (note: the participants will receive usual care also during the exercise intervention period).

### Statistical analysis

2.5

Data will be presented as mean and standard deviation or 95% confidence interval unless otherwise stated. Normality of distribution will be assessed by the Shapiro–Wilk test. To analyze the effect of VBRT on all outcomes in the whole sample (primary objective), linear mixed-effect models (LMM) will be fitted using Restricted Maximum Likelihood (REML) estimation. The model will include time as a fixed effect and participant ID as a random effect. The control period will be included in the LMM as an additional time level. This will allow for the comparison of change during the non-exercise period against the time-adjusted changes observed during the VBRT intervention. For the secondary analysis, between-group differences after the VBRT (secondary objective I) will be assessed using the same LMM framework and including time and group (10% vs. 20 VL) as fixed effects, and participant ID as a random effect. The residual effects derived from the VBRT program after 6 months of follow-up will be analyzed similarly, with time as a fixed effect and participant ID as a random effect. To preserve Intention-to-Treat (ITT) principles, training adherence will not be included in the primary model. A secondary per-protocol sensitivity analysis using LMM with REML estimation will be conducted across all objectives, including only participants who completed ≥80% of the exercise sessions. Pairwise comparisons will be adjusted using the Bonferroni method. Cohen’s *d* effect sizes will be calculated using the pooled baseline standard deviation and interpreted as: trivial (<0.20), small (0.20–0.49), moderate (0.50–0.79), and large (>0.80). Statistical analyses will be conducted using SPSS (version 26.0, SPSS Inc., United States), and the level of significance will be set at α = 0.05.

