While traditional RT investigations in older people maximize physiological adaptations through continuous, rigid periodicity and control over short periods of time (e.g., 10 weeks), pragmatic interventions (i.e., adapted to the individuals’ routines and calendar) but longer in time (e.g., >6 months) are needed to elucidate the real-world effectiveness of exercise interventions during aging. Moreover, understanding whether VBRT can induce residual beneficial effects after exercise program cessation (Buendía-Romero et al., 2025) is crucial for designing cost-effective exercise programs in nursing homes with long-term benefits.

Against this background, the present protocol aims to describe a study designed to i) analyze the effects of one season (from Autumn to Summer; 9 months) of VBRT on skeletal muscle size, muscle function, physical performance, disability, cognitive function and frailty in older adults living in nursing homes (primary objective); ii) compare the impact of different VL thresholds (10% vs. 20% VL) (secondary objective I); and iii) determine the residual effect of the VBRT program after 6 months of exercise cessation (secondary objective II).

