### Design and participants

2.1

This study protocol was registered in ClinicalTrials.gov (ID: NCT07027397) and approved by the Clinical Research Ethics Committee of the Toledo Hospital Complex (ID: 710P). The present protocol will be conducted in accordance with the SPIRIT (Standard Protocol Items: Recommendations for Interventional Trials) statement (Chan et al., 2013; Supplementary Table S1). Adults aged ≥65 years living in two nursing homes (Toledo, Spain) will participate in this research. Participants will be informed about the characteristics of the study and will provide their signed consent. The study will include a 4-week control period, followed by 9 months of VBRT in the leg press exercise and a 6-month follow-up in which no exercise intervention will be conducted. All participants will be allocated into the intervention group due to ethical reasons (Izquierdo et al., 2025), and thus the control period will serve as the comparator condition. Participants will be randomized in two experimental groups: 10%VL group or 20%VL group. A randomization sequence stratified by theoretical maximal isometric force (F_0_) and sex will be used to assign participants to both groups.

Following our intentionally pragmatic and translational perspective to investigate the effects of VBRT on skeletal muscle size, muscle function, physical performance, disability, cognitive function, and frailty, the exercise intervention will be conducted over a whole season, including periods in which the intervention will be paused (e.g., Christmas, Easter, summer holidays) and then restarted. Thus, the main outcomes will be assessed at six specific time points as detailed in Figure 1: prior to a 4-week control period (Pre-control), at baseline (T0), post 6 weeks (T1), post 12 weeks (T2), post 23 weeks (T3), and post 39 weeks (T4). Upon completion of the VBRT, a final follow-up will be conducted after 6 months of usual care (T5).

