**FIGURE 1 F1:**

Experimental design overview. The study comprises three phases: a 4-week control period, a 9-month velocity-based resistance training (VBRT) intervention and a 6-month follow-up period. Assessment time points are indicated at specific weeks (w): T0 indicates baseline; T1-T4, intervention assessments; and T5, final follow-up.

The required sample size was determined on the basis of muscle function, using the 5-rep sit-to-stand (STS) muscle power test (Alcazar et al., 2018). According to previous research conducting exercise interventions in nursing home residents (Gutiérrez-Reguero et al., 2024), a within-group difference of +0.64 W·kg^−1^ (95%CI: +0.39 to +0.89) in relative muscle power was expected. Using this effect size (ES = 0.91), a required sample size of 15 participants was calculated in the G*Power software, assuming α = 0.05 and power = 90%. Assuming a maximum loss to follow-up of ∼35%, we will recruit 27 nursing home residents aged ≥65 years to address our primary objective. Exclusion criteria will include: i) uncontrolled hypertension, unstable or exercise-induced angina pectoris or myocardial ischemia or any other medical condition incompatible with physical exercise, ii) bedridden or unable to walk with assistance, and iii) terminal illness. The study will be performed in accordance with the Helsinki Declaration.

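### The primary objective covers every outcome with no primary outcome or contrast named, and the stated 90% power does not carry over to Bonferroni-adjusted visit comparisons

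*Protocol article*

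**What the plan says.** The Introduction puts six domains under the primary objective: "skeletal muscle size, muscle function, physical performance, disability, cognitive function and frailty in older adults living in nursing homes (primary objective". Section 2.5 (Statistical analysis) does the same for the models: "To analyze the effect of VBRT on all outcomes in the whole sample (primary objective". Section 2.2 refers the reader to Table 1 for the outcomes, and the table does not rank them.

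Section 2.5 sets one significance level ("the level of significance will be set at α = 0.05") and one multiplicity step: "Pairwise comparisons will be adjusted using the Bonferroni method". The primary model has time as its only fixed effect, and "The control period will be included in the LMM as an additional time level". Section 2.1 states that "the main outcomes will be assessed at six specific time points as detailed in Figure 1", namely Pre-control and T0 to T4. T5 follows six months after training ends.

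The sample size text, placed after the Figure 1 caption, reads: "The required sample size was determined on the basis of muscle function, using the 5-rep sit-to-stand (STS) muscle power test". It uses a within-group effect size of 0.91 for relative power, α = 0.05 and 90% power. This gives 15 participants, with 27 to be recruited against a loss of up to about 35%. The Discussion labels only the comparison of 10% with 20% velocity loss as exploratory.

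**The concern.** Three statements in the same article do not fit together: what is primary, what was sized, and what is adjusted.

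- **Sizing against testing.** The trial was sized for one test of one outcome at 0.05. The analysis section applies Bonferroni to pairwise comparisons and exempts no contrast. If the sized contrast is one of many visit pairs, it is tested at a much smaller alpha than the one used to reach n = 15.
- **Error across outcomes.** No outcome is ranked above another and no visit is designated, so a significant visit pair in any of some 20 outcomes could be reported as meeting the primary objective. The adjustment works within each outcome and does not limit that.

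At stake are the stated 90% power and a clear criterion for whether the primary objective was met.

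**Working it through.** **Inputs from the article.** Effect size 0.91, α = 0.05, power 90%, n = 15, 27 recruited, loss about 35%. The six visits in section 2.1 give 6 × 5 / 2 = 15 pairs; with T5, 7 × 6 / 2 = 21 pairs. Table 1 without its three anthropometric rows: muscle size 3, sit-to-stand power 3, force-velocity 4, physical performance 5, disability 2, cognition 1, frailty 2, in total 20.

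**Assumptions.** The Bonferroni family is all visit pairs of the primary model; the article does not list the pairs. The effect size is the mean change divided by the SD of change. The article does not say so, but n = 15 reproduces on that reading. Correlations between outcomes are not given, so a range is shown.

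**Step 1: the plan's own figure.** Paired t-test power comes from the noncentral t with n − 1 degrees of freedom and noncentrality 0.91 × √n. At two-sided 0.05, n = 14 gives 88.2% and n = 15 gives 90.6%. The stated 15 is reproduced.

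**Step 2: the same outcome under Bonferroni.** With 15 pairs, α = 0.05 / 15 = 0.0033; with 21 pairs, 0.05 / 21 = 0.0024. Expected to remain: 27 × 0.65 = 17.55, so 17 or 18. The first figure in each cell is the paired t-test. The second approximates the mixed model by pooled degrees of freedom, (n − 1)(visits − 1), with the same standard error.

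| Evaluable n | 15 pairs | 21 pairs |
|---|---|---|
| 15 | 52% / 69% | 47% / 65% |
| 17 | 62% / 76% | 57% / 73% |
| 18 | 67% / 80% | 62% / 77% |
| 27 | 92% / 96% | 90% / 95% |

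By paired t, keeping 90% power under 15 pairs needs 26 evaluable participants, or 26 / 0.65 = 40 recruited. Under 21 pairs it needs 28, or 44 recruited.

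**Step 3: error across outcomes.** Three quantities must be kept apart. All are two-sided and assume no true effect on any outcome.

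- One Bonferroni-adjusted contrast in each of 20 independent outcomes: 1 − (1 − 0.05/15)^20 = 6.5%.
- Any of the 15 adjusted visit pairs in any of 20 outcomes. Simulation with six visits, n = 15 and pooled degrees of freedom gives 3.6-3.9% per outcome. Over 20 outcomes it gives about 52-55% if independent, 47% at correlation 0.3, 38-39% at 0.5 and 27% at 0.7.
- The omnibus time test of each outcome at 0.05: 1 − 0.95^20 = 64% if independent, and 54%, 42% and 29% at correlations 0.3, 0.5 and 0.7.

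**Step 4: after the fix.** One outcome and one contrast at two-sided 0.05 has 5% error and the power in step 1: 90.6% at n = 15 and 94.0% at n = 17.

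**The case against.** **The inflation may be overstated.** A reader might infer a 64% chance of a false positive at one time point. The documents do not support that: if Bonferroni reduces power on the sized outcome, it protects every other outcome's contrast too, and the figure for one contrast is 6.5%. The larger figures apply only to any visit pair in any outcome, or to the omnibus tests. They also count apparent harm. In simulation with 15-pair Bonferroni, a false benefit at any of T1-T4 versus T0 in any of 20 outcomes occurred in about 11% of trials if independent and 8% at correlation 0.5. So a claim that a false benefit is likely does not hold. This objection stands and limits the point.

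**The outcomes overlap.** Relative and allometric power both derive from absolute power, four parameters come from one force-velocity line, and the SPPB contains the 5-repetition test. Independence is therefore an upper bound. The correlated figures are still well above 5%.

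**The visit pairs serve a purpose.** One might infer that most pairs, such as T2 versus T3, answer no stated question. The Abstract, however, says the time course of adaptation will be assessed, and the Discussion expects gains to accumulate with longer training. That criticism is not made here.

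**The power loss is conditional.** The family is inferred, the loss concerns pairwise contrasts and not the omnibus time test, a mixed model also uses partial data, and full retention of 27 brings power back to 90% or so. All true. But the article itself plans for a loss of up to about 35%.

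**This could sit in an analysis plan.** Contrast lists and cross-outcome procedures often do. The mismatch among the objective, the alpha, the adjustment and the sizing is, however, printed in this article.

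**Conclusion.** The point holds in a limited form. The article makes all outcomes primary, names no primary outcome or contrast, and sizes the trial for a single unadjusted test that its analysis section does not set apart. If Bonferroni covers 15 visit pairs, power on the sized outcome is 62-80% at the planned retention, against the stated 90%. The range reflects 17 or 18 evaluable participants and the choice between paired-t and pooled degrees of freedom.

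Nothing limits error across outcomes. The chance of at least one false-positive visit pair somewhere is roughly 52-55% under independence and 38-39% at an assumed correlation of 0.5, in either direction. That matters because no contrast is singled out; once one is, the exposure is small. The change should be made, but the issue does not invalidate the design.

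**What to change.** In section 2.5, and to match it in section 2.1:

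1. Name relative 5-repetition sit-to-stand muscle power, T4 versus T0, as the single primary outcome and contrast, tested at two-sided 0.05 and outside the Bonferroni family. This matches the sample size calculation and restores 90.6% power at n = 15 without further recruitment.
2. Keep the planned comparison of control-period change (Pre-control to T0) with intervention change as a pre-specified supporting contrast, because section 2.1 makes the control period the comparator and T4 versus T0 alone would leave it out.
3. Label all other outcomes and visits secondary, including the time course, and report them as estimates with 95% confidence intervals. Confine any Bonferroni or Holm adjustment to these secondary contrasts and state which contrasts form the family.

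The cost is wording, and the other domains lose confirmatory status.

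### The announced comparison of control-period change with training change is not delivered by the named pairwise tests, and the stated 90% power does not cover it

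*Protocol article*

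**What the plan says.** Section 2.1 (Design and participants) allocates every participant to training, on ethical grounds, and states that "the control period will serve as the comparator condition". Assessments are at Pre-control, T0 (after the 4 control weeks), and weeks 6, 12, 23 and 39 of the programme (T1 to T4), with T5 six months after training ends.

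Section 2.5 (Statistical analysis) fits, for the primary objective, a mixed model with time as the fixed effect and participant as the random effect. The control period enters as one more level of time. The stated purpose is: "This will allow for the comparison of change during the non-exercise period against the time-adjusted changes observed during the VBRT intervention". The tests named are pairwise comparisons with Bonferroni adjustment, and "the level of significance will be set at α = 0.05".

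The sample-size paragraph of section 2.1 works from a single pre-post change: "a within-group difference of +0.64 W·kg^−1^ (95%CI: +0.39 to +0.89) in relative muscle power was expected". It continues: "Using this effect size (ES = 0.91), a required sample size of 15 participants was calculated in the G*Power software", "assuming α = 0.05 and power = 90"%. It then says: "Assuming a maximum loss to follow-up of ∼35%, we will recruit 27 nursing home residents aged ≥65 years to address our primary objective".

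**The concern.** Both randomised groups train, so the control period is the only non-exercise comparison in the study. The quantity that uses it is the difference between two changes. Pairwise tests of time levels do not produce that quantity. They produce one test of the control-period change and separate tests of the training changes. Reporting the first as non-significant and a second as significant does not test whether the two differ.

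Two further points follow. *Time-adjusted* suggests that something is done about the unequal intervals (4 weeks against 39), but nothing in the stated model does this. The sizing also refers to a single within-group change, so a reader could credit the comparator result with 90% power that was never calculated for it. At stake is whether the primary result can be described as controlled or is an uncontrolled pre-post change.

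**Working it through.** **Inputs from the protocol.** Effect size 0.91, α = 0.05, power 90%, n = 15, 27 recruited and about 35% loss (section 2.1); random effect for participant, categorical time and Bonferroni (section 2.5). Sidedness is not stated.

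**1. The plan's own figure.** A two-sided paired t-test (noncentral t) with standardised change 0.91 gives 90.6% power at n = 15 and 88.2% at n = 14, so n = 15 reproduces. A one-sided test would need 12. The implied SD of the change is 0.64/0.91 = 0.70 W/kg. Applying 35% loss to 27 leaves 27 × 0.65 = 17.55, so 17 completers are used below.

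**2. What the named tests give.** Pre-control and T0 to T4 are 6 levels, hence 6 × 5/2 = 15 pairs, each with coefficients +1 and −1. The announced comparison is

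(T4 − T0) − (T0 − Pre) = T4 − 2·T0 + Pre,

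with coefficients 1, −2, 1. It is not one of the 15 pairs, but it is a linear contrast that the same model can estimate.

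**3. Power under the model's own covariance.** A random intercept implies compound symmetry. With residual variance σ²:

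- Var(T4 − T0) = (1 + 1)σ² = 2σ²
- Var(T4 − 2·T0 + Pre) = (1 + 4 + 1)σ² = 6σ²
- SD ratio = √(6/2) = 1.732

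Assume that 0.91 applies to T4 − T0 and that the mean control-period change is zero. The standardised contrast is then 0.91/1.732 = 0.525. Two-sided power at 0.05 is 47% at n = 15, 53% at 17 and 75% at 27. With mixed-model degrees of freedom, (n − 1) × 5, it is 52%, 57% and 77%. On the paired-t basis, 90% power needs 41 evaluable participants and 80% needs 31.

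**4. Range.** The documents give neither the SD of the control-period change nor its correlation with the training change. Let r be the ratio of the two SDs (control to training) and ρ the correlation. Then

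SD(contrast)/SD(T4 − T0) = √(1 + r² − 2ρr).

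Compound symmetry is r = 1, ρ = −0.5. The range r = 0.25 to 1 and ρ = −0.5 to +0.25 is assumed.

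| r | ρ | SD ratio | Standardised contrast | n for 90% | Power n = 15 | n = 17 | n = 27 |
|---|---|---|---|---|---|---|---|
| 0.25 | +0.25 | 0.968 | 0.940 | 14 | 92% | 95% | >99% |
| 0.25 | −0.5 | 1.146 | 0.794 | 19 | 82% | 87% | 98% |
| 0.5 | 0 | 1.118 | 0.814 | 18 | 83% | 88% | 98% |
| 1 | +0.25 | 1.225 | 0.743 | 22 | 76% | 82% | 96% |
| 1 | 0 | 1.414 | 0.643 | 28 | 64% | 70% | 90% |
| 1 | −0.5 | 1.732 | 0.525 | 41 | 47% | 53% | 75% |

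**5. The sized change under the plan's own adjustment.** Bonferroni over 15 pairs tests each at 0.05/15 = 0.0033. Power for the single change of 0.91 is then 52% at n = 15, 62% at 17 and 92% at 27. The 90% therefore describes one unadjusted test.

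**The case against.** The strongest reply is that section 2.5 does announce a comparison of changes, and that a model with these time levels can estimate it directly. The Bonferroni sentence sets an adjustment; it does not say that no other contrast will be run. This is a condensed article, and an analysis plan not shown might write the contrast out. All of this stands against a stronger reading that the comparator is never tested, which the documents do not support. It does not remove the point: the article states the comparator, the model, the purpose and the tests, and the tests it names do not serve the purpose.

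A reader might also infer that the comparator contrast is simply underpowered. That depends on unstated quantities. If the 4-week change varies far less than the 39-week change, power can reach 92% even at n = 15. The mixed model also keeps Pre-control and T0 data from participants who later drop out.

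A reader might take *time-adjusted* to mean change per week. Multiplying the 4-week change by 39/4 would bring power to about 6% at n = 15 under compound symmetry. No passage mentions rates or extrapolation, so that figure is no criticism of the plan; it only shows why the term needs a definition.

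Nor does the 90% belong specifically to T4 − T0. Section 2.1 names no time point for the expected change, and the Discussion cites the same source study among those reporting gains after 12 weeks of training.

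Finally, 4 weeks cannot stand in for 39, but that is a limit of a single-condition design chosen openly on ethical grounds, not an analysis error. Usual care also continues during training (section 2.4), and the Pre-control assessment offers some check on retest learning. No contrast removes this limit; it can only be acknowledged.

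**Conclusion.** The concern holds in this form: the comparison that makes the control period a comparator is announced, but the named tests do not deliver it; *time-adjusted* has no defined meaning in the stated model; and the 90% power covers one unadjusted within-group change. The mismatch between purpose and tests follows from the text alone.

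The size of any power shortfall is conditional. It is 47%, 53% and 75% at 15, 17 and 27 participants under compound symmetry, and 47% to 92% at n = 15 over the assumed range, always with zero mean control-period change and 0.91 applied to T4 − T0. What can be said without assumptions about the control period is that the protocol offers no power calculation for this contrast. Because it bears on the primary objective and the only non-exercise comparison, it should be settled before analysis.

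**What to change.** In section 2.5:

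- Pre-specify (T4−T0)−(T0−Pre) as a custom contrast in the existing model, with its 95% CI, for the 9-month effect.
- Add (T1−T0)−(T0−Pre), 6 weeks against 4, as the contrast closest in length. Note that the Discussion expects no short-term change in muscle size, disability or cognition, so a null result there would be unsurprising. The documents give no expected 6-week change in power, so its statistical power cannot be stated from them.
- Define *time-adjusted* or delete it.

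In section 2.1, state that the 90% power applies to one unadjusted within-group pre-post change and not to the comparator contrast, without tying it to T4.

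State also that a 4-week control period cannot account for drift over 39 weeks, so that later changes, including those at T5, are interpreted as within-group changes.

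The cost is wording and two custom contrasts. No new data, assessments or change of model are needed. The downside is a more modest claim for the 9-month and follow-up results.
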